### End Point

The observation and sample collection will be terminated after 28 days after surgery or for reasons of (1) death or if (2) the patient is satisfied with the indications for discharge from the ICU.

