## Abstract

**Introduction:** Fever of unknown origin (FUO) and hemodynamic instability are complications that develop after cardiac surgery combined with cardiopulmonary bypass (CPB) for heart disease. Patients who develop fever with hemodynamic instability after cardiac surgery may have systemic inflammatory response syndrome or sepsis. Cardiopulmonary bypass (CPB) is a technique that temporarily takes over the function of the heart and lungs during cardiac surgery. Recent reports suggest that early bloodstream infections of patients undergoing CPB are due to gram-negative bacteria that are present in the intestinal flora. The theory of intestinal flora translocation has growing evidence. Intestinal ischemia-reperfusion that occurs during cardiac surgery with CPB will induce a systemic inflammatory reaction and may cause intestinal flora translocation. Does this systemic reaction cause sepsis? We therefore propose this protocol to determine whether the changes in the intestinal flora in patients after cardiac surgery with CPB are related to sepsis.

**Methods and Analysis:** This study is a prospective observational case–control study to analyze the variation in the intestinal microflora and metabolites in patients undergoing cardiac surgery with CPB and to observe the outcomes of patients with routine clinical interventions. The control group will include healthy people without intestinal illness. Feces and blood samples will be acquired 1 day before cardiac surgery and within 24–72 h after cardiac surgery, and will be used for genomics and metabolomics analyses. Demographic data describing age, sex, main diagnosis, and past medical history and data related to the CPB time and application of antibiotics are available. Sequential (sepsis-related) organ failure assessment, infection-related laboratory items, infection site, and pathogenic microorganisms, and nutrition, and gastrointestinal function assessment are additionally recorded. Group analysis of data will be conducted according to the outcomes (sepsis vs. non-sepsis and survivors vs. non-survivors).

**Ethics and Dissemination:** This protocol has been ethically approved by the Ethics Committee of Peking Union Medical College (ID: ZS-1612). Informed consent will be obtained before subject enrolment, and data will be stored in a secured database. The results will be submitted to international peer-reviewed journals and presented at international conferences.

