## Method and Analysis

### Study Design

This protocol is designed as a prospective observational case–control study in patients who underwent cardiopulmonary bypass (CPB) due to cardiac surgery. Thirty healthy persons aged between 18 and 85, without digestive system disease, will be selected as the control group. The case group will include patients admitted to the intensive care unit (ICU) after cardiac surgery with CPB, which is performed by the Department of Cardiac Surgery of Peking Union Medical College Hospital. The patients enrolled should be divided into two groups according to their outcomes: one group of non-sepsis patients and the other group of sepsis patients after cardiac surgery. Sample collection will be terminated when each group receives 30 cases. These 60 cases will be regarded as the case group. Additionally, all the patients we observe will be further divided into survivors and non-survivors based on 28-days survival. Feces and blood samples will be obtained at certain time points (Figure 1).

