### Study Population

The inclusion criteria are the following. Patients between 18 and 85 years of age who will undergo extracorporeal circulation during cardiac surgery, will be admitted to the ICU and provide written informed consent. The control group will be 30 healthy persons aged between 18 and 85 without digestive disease. The exclusion criteria are as follows; patients would be excluded if they (1) had a fever before surgery, regardless of the etiological evidence of infection; (2) had anti-infective treatment before surgery; (3) had gastrointestinal surgery that left the digestive system dysfunctional; (4) had a history of CPB in the last 6 months; or (5) rejected or abandoned ICU therapeutic intervention. The control group will be excluded if they are taking certain medications.

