#### Sample Collection

There will be 60 patients enrolled as the case group and 30 healthy people as the control. After fasting for at least 6 h but not more than 10 h, venous blood will be collected by direct venepuncture or established venous access from patients enrolled. Plasma will be taken from the blood and remain in Eppendorf tubes at −80°C for 1 h. Fresh fecal samples will be obtained (sometimes aided by glycerinum) and stored at −80°C before analysis. In the control group, samples will be collected once. In the case group, feces and blood samples will be acquired at the following time points (Figure 1): (1) T1: 1 day before cardiac operation; and (2) T2: within 24–72 h of ICU admission, sampling must be performed before patients start oral feeding.

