#### Grouping by Outcomes

The primary outcome is patients with cardiovascular surgery with CPB and healthy people.

The secondary outcomes are as follows.

After sample collection, the case group will be selected and divided into two groups according to their clinical outcomes.

Sepsis group (sub grouped by suspected or documented infection) and non-sepsis group;Survivors and non-survivors based on the 28-days survival.

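### The T2 window opens at 24 h, but ICU-discharge readiness or oral feeding closes sampling, so patients reaching either point before 24 h cannot give the only postoperative sample

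*Protocol article*

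**What the plan says.** All places are in the Protocol article.

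- **Sample Collection** sets two time points for cases. T1 is the day before the operation. The second reads "T2: within 24–72 h of ICU admission, sampling must be performed before patients start oral feeding".
- **End Point** gives the stopping rule: "The observation and sample collection will be terminated after 28 days after surgery", or at death, "or if (2) the patient is satisfied with the indications for discharge from the ICU". The rule covers sample collection as well as observation, and makes no exception for a T2 not yet taken.
- **Abstract** counts the postoperative window from a different origin: "within 24–72 h after cardiac surgery".
- **Study Population** requires that patients "will be admitted to the ICU and provide written informed consent". It states no minimum ICU stay or minimum time without feeding.
- **Study Design** closes the study by quota: "Sample collection will be terminated when each group receives 30 cases".
- **Grouping by Outcomes** says: "After sample collection, the case group will be selected and divided into two groups according to their clinical outcomes".

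The article does not say whether a patient with T1 but no T2 counts toward the 30, is replaced, or stays in with T1 only.

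**The concern.** T2 is the only sample taken after bypass, so every statement about postoperative flora or metabolites rests on it. Whether it can be taken depends on two facts about the patient's recovery: still needing the ICU, and not yet eating. Both are related to the outcome that defines the comparison groups. Sepsis, as the article defines it, requires an acute rise of at least 2 SOFA points, so septic patients should seldom be discharge-ready or eating by 24 h. Uncomplicated non-septic patients may well be.

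If so, T2 is missing in a way tied to the sepsis versus non-sepsis contrast, and the non-septic patients with T2 recover more slowly than non-septic bypass patients in general. The stated aim, to describe patients after cardiac surgery with CPB, would then be met only for a subset that the eligibility criteria do not declare.

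**Working it through.** **1. The rules side by side.** Let D be the time from ICU admission to meeting ICU discharge indications, and F the time to first oral feeding.

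- Sample Collection: T2 is allowed only between 24 h and 72 h, and before F.
- End Point: no sample is allowed after D.
- Together, T2 is possible only if min(D, F) > 24 h.

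A patient discharge-ready at 20 h has sampling closed 4 h before the window opens. A patient who eats at 18 h and stays in the ICU also has no permitted T2. A patient who reaches either point at 30 h has 30 − 24 = 6 h in which blood and fresh stool can be obtained. T2 is possible there, but only if it is taken in time.

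**2. The Abstract's anchor.** Counting from surgery keeps the 24 h lower bound. Its one relevant difference is that it does not require the patient to be in the ICU.

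**3. Enrolment needed.** The article gives no sample-size derivation and no data on ICU stay or time to feeding, so there is no figure to reproduce. Let f be the share of non-septic patients with min(D, F) below 24 h; f is an assumption throughout. To obtain 30 non-septic patients with T2, n = 30 / (1 − f), rounded up:

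| Assumed f | 30 / (1 − f) | n |
|---|---|---|
| 5% | 31.6 | 32 |
| 20% | 37.5 | 38 |
| 35% | 46.2 | 47 |
| 50% | 60.0 | 60 |
| 70% | 100.0 | 100 |

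At 35%, 46 patients give 46 × 0.65 = 29.9, so 47 are needed.

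**4. How far the sampled patients could differ.** Assume min(D, F) is lognormal with median m and log-scale SD 0.6. The share lost is p = Φ[(ln 24 − ln m) / 0.6]. The median among those who can be sampled is m × exp{0.6 × Φ⁻¹[p + (1 − p)/2]}.

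| Assumed m | Share lost | Median among those sampled |
|---|---|---|
| 24 h | 50% | 36.0 h |
| 36 h | 25% | 43.6 h |
| 48 h | 12% | 52.7 h |
| 72 h | 3% | 73.8 h |

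The shift is always toward slower recovery. Its size runs from negligible to large, and the documents cannot say which applies. Neither table measures bias in the sepsis contrast.

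**The case against.** **Group membership.** A reader might infer that the non-sepsis group itself is selected, with a T2 sample acting as a hidden eligibility criterion. No section says so. The phrase about dividing cases after sample collection may only describe the order of events, and the mixed model planned for cases versus controls can retain patients with T1 only. This stands: selection of membership is conditional. It does not rescue the T2 analyses, because a patient type that can never supply T2 leaves the model nothing but extrapolation at that time point.

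**Prolonged illness.** A reader might also infer a comparator selected for prolonged ICU illness. The text requires only that the patient be neither discharge-ready nor eating at 24 h. Those who recover between 24 h and 72 h can be sampled.

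**Direction.** Bias toward no difference is plausible if both groups are sicker than average, but nothing in the documents establishes it. Narrower generalisability is also not the same as a biased contrast: for the article's question of sepsis versus a purely inflammatory response, non-septic patients still in the ICU at 24 h are a reasonable comparator.

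**The feeding rule.** The Discussion names enteral feeding among the interventions that change intestinal bacteria, so sampling before feeding is a sensible control. If post-feeding samples came mainly from non-septic patients, mixing them in would confound feeding with group. This stands and shapes the fix.

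**Loose wording.** Taken literally, the End Point rule would also end observation before the 28-day survival status that Study Design and Definition need, so it may be a general end-of-follow-up statement. That may be so, but as written it governs sample collection and no other section overrides it.

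**Conclusion.** The conflict is in the text: End Point and Sample Collection together leave no permitted T2 for a patient who is discharge-ready or eating before 24 h. T2 and T1-to-T2 analyses are therefore restricted to patients with at least 24 h of ICU need without oral feeding. The restriction extends to group membership only if patients without T2 are not counted.

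That the loss falls mainly on uncomplicated non-septic patients is an inference from the sepsis definition, not a documented fact. The share lost and the direction of any bias are unknown. The point is worth correcting because the missingness depends on the postoperative course and most of the remedy is cheap. It does not show that the sepsis comparison is invalid.

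**What to change.** 1. Reconcile the Abstract, End Point and Sample Collection. Use one anchor for T2, 24–72 h after surgery as in the Abstract, and state that ICU-discharge readiness does not stop T2, so that a patient moved to the ward can be sampled there.
2. Keep pre-feeding samples as the main T2 analysis. Record when feeding starts, and use any post-feeding sample only as a flagged sensitivity analysis.
3. State whether a patient with T1 but no T2 counts toward the 30. Report the number, baseline features and outcomes of such patients.
4. Flag samples collected before and after the change.

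**Cost.** A short amendment, and ward collection of one stool and one blood sample per affected patient. Recruitment reports 45 of 60 cases collected by 31 January 2020, so from that count a change in sampling could reach at most 60 − 45 = 15 cases, and T2 conditions would vary somewhat between those already collected and the remainder. The report in step 3 can cover all cases. The main analysis will still lack patients who ate before 24 h. That limit is accepted in order to keep feeding out of the main comparison, and it should be stated.

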#### Observation and Data Recording

Demographic data describing age, sex, main diagnosis, and past medical history are available at the inception of the study. Data related to the CPB time and application of antibiotics post-operation are available on the MUL-GM-CSCPB study Data Recording Sheet (Supplementary Table). The following observational data will be measured and recorded when patients are admitted to the ICU and at every sampling time.

Sequential (sepsis-related) organ failure assessment includes blood pressure; mean arterial pressure (MAP); and vasoactive drugs, including noradrenaline (NE), epinephrine (E), and dopamine (Dopa); PaO_2_/FIO_2_; Glasgow Coma Scale score; creatinine or urine output; bilirubin; and platelet count.Infection-related items include body temperature, WBC count, neutrophils, PCT, and antibiotics.Whether to be diagnosed with sepsis (according to Sepsis 3.0).Infection site and pathogenic microorganism.Nutrition and gastrointestinal function assessment including enteral or parenteral nutrition, bowel dilatation tested by ultrasound, gastric residual volume and intra-abdominal pressure measured via bladder.

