#### Definition

The clinical criteria according to the third international consensus (Sepsis-3) (17):

Sepsis: suspected or documented infection and an acute increase of ≥2 SOFA points.

Suspected infection group will be identified as those who had body fluids sampled for culture and received antibiotics but had a negative culture result.

The documented infection group will be identified as those who had body fluids sampled for culture with a positive result.

Survivors: Patients that survive for 28 days or more after surgery.

Non-survivors: Patients that survive <28 days after surgery.

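### Observation ends once a patient meets the indications for ICU discharge, but patients are classified by 28-day survival, and no section shown provides for vital status after that point

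*Protocol article*

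**What the plan says.** The End Point section gives one rule for stopping: "The observation and sample collection will be terminated after 28 days after surgery or for reasons of (1) death or if (2) the patient is" judged ready to leave the ICU. Its last limb reads in full: "or if (2) the patient is satisfied with the indications for discharge from the ICU". The same rule covers observation and sampling, and whichever event comes first ends both.

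The survival grouping runs on a different clock. Study Design says that "all the patients we observe will be further divided into survivors and non-survivors based on 28-days survival". Grouping by Outcomes lists "Survivors and non-survivors based on the 28-days survival" as one of two secondary groupings. The Definition section fixes the two classes: "Survivors: Patients that survive for 28 days or more after surgery" and "Non-survivors: Patients that survive <28 days after surgery". Neither class depends on where the patient is. The Discussion repeats that the sixty patients are enrolled so that 28-day survival or death can be observed, and the Multi-Omic Data Analysis Plan compares the survivor and non-survivor groups.

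On timing of data, Observation and Data Recording says: "The following observational data will be measured and recorded when patients are admitted to the ICU and at every sampling time". Sample Collection sets two sampling times in the case group: the day before surgery (T1) and 24–72 h of ICU admission (T2).

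**The concern.** A patient who meets the ICU-discharge indications before day 28 leaves observation with 28-day status not yet determined. The definitions nevertheless require every observed patient to be placed in one of two classes by that status.

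Two ways of filling the gap suggest themselves, and each changes the question:

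- **Count discharged patients as alive.** The outcome becomes survival to ICU discharge under the name of 28-day survival, and any death on the ward or at home before day 28 is filed as a survivor.
- **Leave discharged patients out.** The comparison becomes ICU deaths against patients still in the ICU at day 28, which is not a comparison of survivors and non-survivors of cardiac surgery.

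The survival grouping is one of the two outcome groupings named in the abstract, and the analysis plan also relates factors to prognosis by logistic regression. With few deaths expected, the grouping has little tolerance for error.

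**Working it through.** The article gives no event count or sample size calculation for the survival grouping, so there is no stated figure to reproduce. The main check compares the rules. The arithmetic only shows scale.

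**Step 1. Can the End Point rule be read as stopping sampling only?** It names observation alongside sampling. The last scheduled sample is T2, at 24–72 h of ICU admission. For a patient who meets the discharge indications after T2, no sample remains to be stopped, so the clause can only end observation.

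**Step 2. Who has an observed day-28 status under the rule?**

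| Course after surgery | Observation ends at | Day-28 status observed? |
|---|---|---|
| Dies before meeting the ICU-discharge indications | Death | Yes, non-survivor |
| Still in the ICU at day 28 | Day 28 | Yes, survivor |
| Meets the discharge indications before day 28, alive at day 28 | Discharge indications | No |
| Meets the discharge indications before day 28, dies before day 28 | Discharge indications | No |

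The last two rows cannot be told apart from the data the rule allows.

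**Step 3. Does another section supply the status?** Data recording is tied to ICU admission and the sampling times. The Discussion states the aim of observing 28-day survival but gives no mechanism. No section shown mentions a check after ICU discharge.

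**Step 4. How many patients could be affected?** The share meeting the discharge indications alive before day 28 is not stated. Under assumed shares, out of the 60 cases in Study Design:

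- 50%: 60 × 0.50 = 30 without observed status
- 80%: 60 × 0.80 = 48
- 95%: 60 × 0.95 = 57

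**Step 5. How many deaths are expected?**

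- Reference case, using the 3% in-hospital mortality cited in the Introduction: 60 × 0.03 = 1.8 deaths. The chance of none is 0.97^60 = 0.16.
- Sample as designed, 30 sepsis and 30 non-sepsis patients, with sepsis mortality assumed at 10–30% and 3% in the others: 30 × 0.10 + 30 × 0.03 = 3.9, up to 30 × 0.30 + 30 × 0.03 = 9.9.

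**Step 6. What is one misclassified death worth?**

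- Sample as designed: 1/9.9 = 10% to 1/3.9 = 26% of the expected non-survivors.
- Reference case: 1/1.8 = 56%. This treats the sample as unselected, which Study Design rules out by fixing 30 sepsis cases, so it should not be merged with the range above.

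**Step 7. How many deaths might be missed?** The share of 28-day deaths that fall after the discharge indications are met is not stated. If it is assumed to be 10–50%:

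- Reference case: 1.8 × 0.10 = 0.18 to 1.8 × 0.50 = 0.9.
- Sample as designed: 3.9 × 0.10 = 0.39 to 9.9 × 0.50 = 4.95.

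**Step 8. Direction of error.** If discharged patients default to alive, every recorded non-survivor is a true death before day 28. The non-survivor group is incomplete but not mixed. The survivor group is the one that takes in misclassified patients.

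**The case against.** The strongest reply is that the investigators plainly intend to know 28-day survival. The Discussion says so, and the fault is probably loose wording in End Point. The Data Recording Sheet (a supplementary table) and Figure 1 are not shown, and either may carry day-28 status. How vital status is obtained is also a detail that a condensed article may leave to the full protocol. This stands as far as it goes: the absence of a described procedure is not itself the fault. What remains is a stated stopping rule that, followed literally, excludes the follow-up that the definitions need. An intent stated elsewhere sharpens that conflict and does not resolve it.

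A second reply is that the case–control contrast and the sepsis contrast do not use day-28 status, and that the survivor comparison would be weak with so few deaths even under perfect ascertainment. That also stands, and it limits how serious the point is.

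Three stronger readings are tempting, and the documents do not support them:

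- **That the survivor and non-survivor groups cannot be built at all.** They can be built in part (the first two rows of the table), and the missing status is probably recoverable from records.
- **That the non-survivor group is contaminated.** Step 8 shows that any contamination falls on the survivor group.
- **That the exclusion of patients who "5) rejected or abandoned ICU therapeutic intervention" makes the survival outcome biased.** Abandonment may become known only after enrolment, but refusal can be known at the outset. Nothing in the article links either to prognosis. Whether to keep such patients is a question of target population, separate from the conflict described here.

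**Conclusion.** The conflict is real and is in the current text. End Point stops observation when the ICU-discharge indications are met. Study Design, Grouping by Outcomes, Definition and Discussion need status at 28 days after surgery for all observed patients. Taken literally, the rule leaves that status unobserved for everyone who meets the indications earlier.

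This conclusion rests on the wording alone and needs no assumption. Its numerical size does need assumptions, because neither the share leaving before day 28 nor the number of later deaths is given. With 3.9 to 9.9 deaths expected under the assumed sepsis mortality, one misclassified death is about 10–26% of the non-survivor group. No document figure shows that such a death will occur.

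The point should be corrected, but it does not block the study. It affects one of two secondary groupings, and the data are likely to be retrievable.

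**What to change.** Reconcile End Point with Study Design, Grouping by Outcomes, Definition and Discussion:

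1. Limit the ICU-discharge stop to sampling and bedside data collection.
2. State that vital status at day 28 after surgery is obtained for every enrolled patient, wherever the patient is, from the hospital record or by one contact.
3. Obtain the same item retrospectively for the 45 cases that Recruitment reports as collected by January 31, 2020.
4. Where this cannot be done, rename the outcome as status at ICU discharge and change the definitions of the two groups to match.

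If the full protocol or the Data Recording Sheet already provides for day-28 status, only the wording of End Point has to change.

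The cost is a short amendment, one record check or call per patient, and a check that the consent covers the contact. No patients or samples are added. It is better done soon, because status becomes harder to recover with time.
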